#### Timing and frequency of analyses

A single principal analysis is planned six months after the last person is recruited. If considered appropriate, follow-up of recruits will be extended at this time. The Data Monitoring Committee (DMC) (see below) will determine the frequency o- confidential interim analyses.

#### Secondary sub-group analyses

Planned subgroup analyses include:

(i) Under-nourished, normal or obese;

(ii) Patient groups (medical, or surgical (including trauma));

(iii) Age <65 or ≥ 65;

(iv) Evaluation by the severity of illness, including; APACHE II and SOFA scores, above and below mean or median score; and

(v) Severe sepsis/septic shock on recruitment

Stricter levels of statistical significance (2p < 0.01) will be sought, reflecting the exploratory nature of these subgroup analyses. The Chi-squared test for heterogeneity will be used to explore any apparent differential effects.

#### Economic analysis

The underlying aim is to keep economic data collection as parsimonious as possible to minimise the burden upon trial participants and participating centres. Data on costs to the NHS including treatments, investigations and consultations will be collected as part of the economic evaluation. The type of economic evaluation performed will depend upon the findings [23]. Both deterministic and stochastic sensitivity analysis [27] will be used to explore the importance of the uncertainty surrounding estimates of effectiveness, cost, and cost-effectiveness/utility. NHS resource use will be costed using appropriate unit costs. These will be taken from published sources (e.g. drug costs from the British National Formulary and GP cost from published estimates [28], manufacturers' list prices (e.g. consumables, equipment)) or using study-specific estimates. QALYs will be calculated using the EQ5D scores [29]. The EQ5D has been successfully used to measure changes in quality of life in patients discharged from ICU [30].

### Power calculation

The primary endpoint for the trial is the proportion of patients acquiring infection(s) after starting trial PN. Systematic reviews indicate that the reduction in proportion of patients acquiring infections in previous trials ranged from approximately 50% in the control arm to 40% in the intervention arm. Removing Griffiths' glutamine trial [31,32] – which only reported infections in a post-hoc analysis – shows the effect may indeed be greater (from 50% in the control arm to 30% in the intervention arm). A plausible reduction to detect would be the midpoint of these two estimates (i.e. a reduction from 50% to 35%), hence 340 participants would be required to detect this size of difference (with 80% power and 2p < 0.05) [33].

Given the high mortality rates in critical care patients [1], we have allowed for potential loss of patients to follow-up over the six months (see below – this would primarily affect secondary outcomes such as quality of life measures). We have consequently inflated the sample size requirement by approximately 20%, thus plan to recruit 500 patients to the trial.

Based on routine data available from the Scottish Intensive Care Society (SICS) audit database, the average length of ICU stay for patients receiving PN is approximately 9 (SD 7) days. For a 2 day reduction in ICU stay to be detected, with 80% power and 2p < 0.05, a trial of approximately 400 patients would be required. As we do not expect any dropout from the trial prior to discharge, we are adequately powered to detect this level of change.

A trial with 500 patients would allow us to detect a quarter of a standard deviation (0.25SD) change in hospital length of stay with 80% power and 5% significance (assuming all data for length of stay are available).

A trial of 340 patients would have 80% power and 5% significance to detect differences in Quality of Life measures of approximately 0.33SD (a third of a standard deviation change) or 90% power to detect a 0.5SD change. Previous research in the behavioural field suggests that a 0.5SD change is the level of change that should be associated with a moderate change in quality of life measures [34,35]. As such we are well powered to detect meaningful changes in quality of life measures.

#### Recruitment rates

Approximately 900 patients per annum receive PN in Scottish Intensive Care Units (source: SICS audit database). Assuming a conservative recruitment rate – that we recruit a third of eligible patients – we expect to recruit the 500 patients required within a two-year recruitment phase.

### Data analysis

Analysis of dichotomous outcomes will be analysed using statistical tests such the Chi-squared test. Continuous measures will be analysed using t-tests (with transformation of data to Normality if appropriate), or non-parametric equivalents. A further analysis accounting for the inter-relationship between deaths and length of stay will be undertaken, akin to that described for ventilator-free days by Rubenfield [26] mentioned earlier. This, for example, would allow the apparently short length of stays associated with early deaths to be accounted for appropriately. A significance level of 2p < 0.05 will be considered as evidence of statistical significance for the primary outcomes. Confidence intervals will also be presented where appropriate. The economic analysis will incorporate sensitivity analysis, and confidence intervals will be constructed around stochastic cost data using techniques such as bootstrapping [27].

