### Treatment allocation

The existing central randomisation service (fully automated computerised telephone randomisation) in the Health Services Research Unit at the University of Aberdeen will be used to randomise patients. Recruiting staff will telephone the randomisation line and will be asked to key in details of identification and important prognostic factors (see below), when confirming eligibility and consent. Consent procedures will adhere to the 2003 Mental Health (Care and Treatment) (Scotland) Act. Random allocation to one of the four possible treatment combinations (see above) will be minimised on trial centre; age (<65 years or ≥ 65 years); sex; patient groups (medical or surgical (including trauma)); and, patient nutritional status (under-nourished, normal or obese – subjective clinical assessment [24]. A four digit number for that patient will be provided by the automated randomisation service, the research nurse accessing the randomisation service will then inform the centre pharmacy of this randomisation number. The trial office, based at the University of Aberdeen will have provided each pharmacy with a list of these random numbers linked to one of the four treatment allocations, thus maintaining the blinding of local investigators to the trial treatment. Figure 1 summarises these arrangements.

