### Analysis plans

#### Ground rules for the statistical analyses

The statistical analyses will be based on all people randomised, irrespective of subsequent compliance with nutritional support. The principal comparisons will be:

(i) all those randomised glutamine versus all those not allocated glutamine

(ii) all those randomised selenium versus all those not allocated selenium

(iii) all randomised glutamine and selenium versus all randomised glutamine alone versus all randomised selenium alone versus all randomised placebo

Evidence will be sought for an interaction between glutamine and selenium.

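### Allocation is minimised on five prognostic factors but the tests named for the outcomes use none of them, so p-values and intervals are somewhat conservative and a modest gain in precision goes unclaimed

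*Protocol article*

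**What the plan says.** Treatment allocation (protocol article): "Random allocation to one of the four possible treatment combinations (see above) will be minimised on trial centre", followed by age group, sex, medical or surgical group, and nutritional status in three categories. The same section describes what recruiting staff key in as "important prognostic factors (see below), when confirming eligibility and consent".

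Ground rules for the statistical analyses: the first principal comparison is "all those randomised glutamine versus all those not allocated glutamine". The second is the same contrast for selenium, and the third compares all four groups. An interaction between the supplements will also be looked for. No covariates are mentioned.

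Data analysis: "Analysis of dichotomous outcomes will be analysed using statistical tests such the Chi-squared test" and "Continuous measures will be analysed using t-tests (with transformation of data to Normality if appropriate), or non-parametric equivalents". For the criterion: "A significance level of 2p < 0.05 will be considered as evidence of statistical significance for the primary outcomes".

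Secondary sub-group analyses: three of the five factors (nutritional status, patient group, age) appear, but only to define subgroups for heterogeneity tests. Centre and sex have no stated part in any analysis.

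Power calculation: for infection, 50% against 35%, "hence 340 participants would be required to detect this size of difference (with 80% power and 2p < 0.05"; the recruitment target is 500.

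**The concern.** Minimisation makes the arms more alike on the chosen factors than simple randomisation would. If those factors predict outcome, the treatment difference varies less from one hypothetical repetition of the trial to the next. The usual variance formulas behind the Chi-squared and t-tests do not know this. They still include the part of the outcome variation that the allocation has balanced out, so the reported standard error is larger than the true one.

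The consequence is a loss of calibration and efficiency. The test at 2p<0.05 rejects a true null less often than 5% of the time, intervals for infection and mortality are wider than they need be, and a real effect is somewhat more likely to be missed than under an analysis that uses the factors. The variables needed are already recorded at randomisation.

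**Working it through.** **Inputs from the article.** Infection 50% versus 35%; two-sided 5%; 80% power; 340 required and 500 planned; 10 recruiting sites (Discussion); the five minimisation factors. Equal numbers at each margin of the factorial are assumed.

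**Input not in the article.** R², the share of outcome variance explained by the five factors. I take 4% to 14% as the working range and show values outside it below.

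**1. The plan's own figure.** With p̄ = 0.425,

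n per group = [1.96·√(2·0.425·0.575) + 0.8416·√(0.50·0.50 + 0.35·0.65)]² / 0.15² = (1.370 + 0.582)² / 0.0225 = 169.3, rounded up to 170.

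That gives 340 in total, exactly as stated. The sample size therefore rests on an unadjusted comparison of two proportions.

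**2. True size of the unadjusted test.** With near-complete balance on the factors, true SE = reported SE × √(1−R²), so

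true size = 2·[1 − Φ(1.96/√(1−R²))].

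| R² | reported SE / true SE | true size of nominal 5% test |
|---|---|---|
| 0.02 | 1.010 | 4.8% |
| 0.04 | 1.021 | 4.5% |
| 0.14 | 1.078 | 3.5% |
| 0.20 | 1.118 | 2.8% |
| 0.30 | 1.195 | 1.9% |

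**3. Power for 50% versus 35%.** Let t = 0.15/√(0.425·0.575·4/N), which is 2.798 at N=340 and 3.392 at N=500.

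Unadjusted power = Φ((t − 1.96)/√(1−R²)); adjusted power = Φ(t/√(1−R²) − 1.96).

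| N | R² | unadjusted | adjusted | gain (unrounded inputs) |
|---|---|---|---|---|
| 340 | 0.04 | Φ(0.855) = 80.4% | Φ(0.895) = 81.5% | 1.1 points |
| 340 | 0.14 | Φ(0.903) = 81.7% | Φ(1.057) = 85.5% | 3.8 points |
| 500 | 0.04 | Φ(1.462) = 92.8% | Φ(1.502) = 93.4% | 0.5 points |
| 500 | 0.14 | Φ(1.545) = 93.9% | Φ(1.698) = 95.5% | 1.6 points |

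Outside that range, at N=500: 92.6% to 92.9% for R² = 0.02, and 94.5% to 96.7% for R² = 0.20.

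**4. Equivalent number of patients.** The unadjusted test under minimisation matches adjusted power at 500 when t_N = t_500 + 1.96·(1 − √(1−R²)).

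- R² = 0.04: t_N = 3.392 + 0.040 = 3.432, so N = 500·(3.432/3.392)² ≈ 512, or 12 more.
- R² = 0.14: t_N = 3.392 + 0.142 = 3.535, so N ≈ 543, or 43 more.

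**5. Simulation check.** Four-arm minimisation on the five factors was simulated with 10 unequal centres and probability 0.8 of taking the best-balancing arm (both assumptions). The Chi-squared test was compared with a logistic model containing the five factors. Under the null at N=500 (2,500 trials, simulation error about 0.4 points):

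| R² | size, unadjusted | size, adjusted | mean reported SE | actual SD of the difference |
|---|---|---|---|---|
| 0 | 5.5% | 5.4% | 0.0446 | 0.0447 |
| about 0.07 | 4.5% | 5.0% | 0.0446 | 0.0434 |
| about 0.20 | 2.7% | 4.8% | 0.0446 | 0.0401 |

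Under 50% versus 35% (1,000 trials each), power rose from 77.8% to 79.6% (N=340, R² about 0.06), 83.9% to 87.3% (N=340, R² about 0.15), 93.5% to 94.5% (N=500, R² about 0.06) and 94.9% to 96.7% (N=500, R² about 0.13). Simulation error is about 1 point. The 77.8% sits roughly two such errors below the formula; the gains agree with step 3.

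**The case against.** **The method may be settled elsewhere.** The analysis plan is not shown, this is a condensed article, and its wording offers the Chi-squared test as an example. That stands in part: a reader might infer that the protocol rules out adjustment, and it does not. But the Data analysis section is not silent. It names methods and a significance criterion for the primary outcomes, every named method is unadjusted, and the sample size follows an unadjusted formula. The point is a better choice than the one stated, not a missing detail.

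**A conservative test makes no false claims.** This stands. A reader might infer that ignoring the minimisation factors invalidates the tests or inflates type I error; the calculation shows the opposite direction.

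**Nothing promised is lost.** This also stands. By formula the unadjusted test has 80.4% to 81.7% power at 340 over the working range, against 80% planned, and about 93% to 94% at 500. It is likewise tempting to say that the balance is wasted. It is not: the actual SD of the estimate falls (0.0401 against 0.0446 reported at R² about 0.20). What is lost is credit for that precision in the standard error.

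**The patient equivalent is easily overstated.** Computing 500/(1−R²) gives 521 to 581, or about 20 to 80 extra patients. That compares adjustment with an unadjusted test under simple randomisation, not with the minimised allocation used here.

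**Prognostic strength is unknown.** True. With R² = 0 there is nothing to gain, although the article itself calls the factors prognostic.

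**Conclusion.** The concern holds as a modest matter of efficiency and calibration, not of validity. The allocation uses five factors and the named analysis uses none, so if the factors predict outcome the reported standard errors are too large, by about 2% to 8% for R² of 0.04 to 0.14. At the planned 500 patients the practical gain for the design effect is small, and it comes at almost no cost.

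The figures rest on an assumed R², near-complete balance from the minimisation, equal margins, and the plan's 50% versus 35%. For the binary outcomes the gain lies in power, correct size and the standard error of the risk difference; the standard error of an adjusted log odds ratio need not be smaller than the unadjusted one. Leaving the other supplement out of each marginal comparison is not a separate fault, since the four-group comparison and the interaction are already planned.

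**What to change.** In the Data analysis section, name as principal analysis of infection and of mortality a logistic model with indicators for glutamine and selenium and the five minimisation factors. Report a standardised risk difference with 95% CI alongside the adjusted odds ratio, so that the result can be read on the scale used for the sample size. Use the same covariates in a linear model for continuous outcomes. Keep the Chi-squared and t-tests (or rank-based equivalents) as supporting unadjusted results, and say in advance which result is principal.

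Cost: a sentence or two of text. All five factors are captured at randomisation, so there is no new data collection and no change to the sample size. The one practical point is small centres, which should be pooled by a rule fixed beforehand or handled with centre as a random effect.

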### Organisation

#### Local organisation

Each collaborating centre will identify a principal investigator. The responsibilities of this person will be to:

1. establish the trial locally (for example, by getting agreement from clinical colleagues, facilitating local research ethics committee and trust approval; identifying and appointing a local study nurse; and ensuring that all clinical staff on ICU and the hospital pharmacy are aware of this trial)

2. agree to follow the trial protocol and to ensure that all team members on his/her site understand their obligations and to conduct the trial to GCP requirements

3. ensure that all study site personnel are adequately trained and qualified to carry out their delegated responsibilities and provide support and supervision to these personnel

4. agree not to start the trial until Main REC, LREC and local management approval is given

5. retain all documentation associated with the trial and all documentation sent by the Chief Investigator or Sponsor of the trial

6. report deviations from the protocol to the Chief Investigator

7. report any safety issues to the Chief Investigator

8. take responsibility for clinical aspects of the trial locally (for example, if any particular concerns emerge)

9. notify the Trial Office of any unexpected clinical events which might be related to trial participation

10. report serious adverse events to the Chief Investigator within 24 hours of the Principal Investigator knowing of the serious adverse events

11. provide support and supervision for the local study nurse

12. represent the centre at collaborator's meetings

Each clinical centre may appoint a ***study nurse ***to co-ordinate the day to day aspects of the trial. The responsibilities of this person will be to:

1. keep local staff informed of progress in the trial

2. keep regular contact with the local principal investigator, with notification of any problem or unexpected development

3. maintain regular contact with the Trial Office

4. identify potential participants and keep a log of whether or not they are recruited (with reasons for non-participation)

5. liaise with PN team

6. check eligibility, give information about the trial, and seek consent

7. randomise patients and obtain randomisation code

8. liaise with the hospital pharmacy

9. collect data describing participants, and send these to the Trial Office

10. liaise with consultants on other wards after patients have been discharged from ICU

11. record outcome measures on study CRFs

12. send study CRFs to Trial Office no more than eight weeks after each patient has been recruited

13. clarify the situation when the Trial Office fails to make a contact with a local participant, getting in touch by telephone

14. seek further clinical details when a major trial event (such as a hospital admission or death) is reported to the Trial Office, even if this occurs in another hospital

15. provide support for participants in other ways if there are difficulties

16. represent the centre at trial nurse meetings and collaborators meetings

Each clinical centre will designate ***study pharmacist(s) ***to co-ordinate the day-to-day pharmacy aspects of the trial. The responsibilities of the local pharmacists will be to:

1. allocate treatment for the patient according to the assigned randomisation code using the SIGNET randomisation schedule

2. ensure the allocation is checked by a pharmacist (other than ICU pharmacist if possible)

3. formulate the PN according to prescription, stability information and hospital SOPs

4. label bags appropriately to ensure blinding of treatment allocation is maintained at ward level

5. ensure that clinical trials pharmacists and aseptic pharmacists are the only personnel on site unblinded to treatment allocation

6. record the use of the SIGNET study PN bags and selenium if applicable on the accountability log

7. record the use of bags after every patient has completed their SIGNET PN on the pharmacy stock control website

8. ensure that all study site pharmacy personnel are adequately trained and qualified to carry out their delegated responsibilities and provide support and supervision to these personnel

9. manage stock levels to ensure sufficient stock of both glutamine and non glutamine bags to provide seven days of SIGNET PN when patient recruited

10. ensure that the storage conditions of the Signet Study PN bags are adhered to

11. ensure that there is stability data available for all variations in the electrolyte profiles of the Signet Study PN bags that are used

12. retain all documentation associated with the trial for example patient worksheets, completed prescriptions, study drug accountability logs, shipping receipt, destruction or disposal documentation, temperature control logs and all documentation sent by the Chief Investigator or Sponsor of the trial

13. report deviations from the protocol to the Principal Investigator

14. report any safety issues to the Principal Investigator

### Trial co-ordination

#### The Trial Office

The Trial Office is in the Centre for Healthcare Randomised Trial (ChaRT), in the University of Aberdeen, which gives day-to-day support to all clinical centres. It is responsible for collection of data (in collaboration with the local study nurses), data processing and analysis. It is also responsible for randomisation and unblinding, (as clinically necessary). The trial coordinator is based in Edinburgh and will supervise the day-to-day conduct of the trial under the direction of the Chief Investigator and the Director of CHaRT. The Trial Office will be responsible for submitting annual reports to MREC, MRC, and regular reporting of SSARs and SUSARs to MREC and MHRA. It will also produce progress reports to both the Trial Steering Committee, and unblinded interim reports to the Data Monitoring Committee (DMC).

There will be four staff directly located in the central Trial Office – the data manager/secretary, the statistician, the economist and the programmer. These staff members will be supported by senior members of CHaRT (The Director, the Senior Trial Manager and the Senior IT Manager and by the Director of HSRU and grantholder). The *trial co-ordinator *will be based in the University of Edinburgh but will be in day to day contact with the trial office and will be collocated in the trial office four days a month.

The *trial co-ordinator *will take overall responsibility for the day to day conduct of the trial, including supervision of all trial staff, visiting all centres and working with the local ICU investigators to establish the trial, providing regular liaison with the research nurses, arranging all trial meetings, and reporting to the project management group. The *data manager/secretary *will be responsible for all aspects of data collection and processing, including processing of trial entry data, data entry, questionnaire monitoring, chasing missing information, and follow-up of non-responses. The *programmer *will establish a database management system for efficient conduct of the trial including the randomisation, timely despatch of questionnaires, automatic form monitoring, data validation and cleaning. The *statistician *will undertake all statistical tasks in the study including the formal analysis and reporting of the data, progress reports to the Study Committees at study end, all under the supervision of the Director of HSRU (one of the grant holders).

A *health economist *will be responsible, under the supervision of the Senior Health Economist (one of the grant holders), for the development of data collection forms (such as the patient/carer time and travel questionnaire) required for the economic evaluation; the unit costs of health care resources; the analysis of the economic data; and the preparation of the economic evaluation component of the final report.

